## Methods: participants, interventions and outcomes

### Study setting

Six palliative and/or cancer care centres in metropolitan New South Wales (NSW), Australia will be involved in the trial. Details about participating sites can be obtained from the trial web address: http://www.ANZCTR.org.au/ACTRN12618001103257.aspx.

### Eligibility criteria

#### Sites

All participating sites must nominate a contactable ‘clinical champion’ with whom the project team can liaise directly.

#### Participants

All medical and nursing personnel (‘clinicians’) routinely caring for cancer and/or palliative care patients at a participating site are eligible to participate in the study. Participants must be willing to give written informed consent and be willing to participate in and comply with the study policies and procedures.

### Exclusion criteria

#### Sites

A competing trial that is enrolling cancer and/or palliative care clinicians.

#### Participants

Agency and/or casual nurses or physicians who have worked less than one shift in the month before the intervention commences and unregistered health professionals who are unlikely to be undertaking and documenting patients’ pain assessment.

### Intervention

#### Intervention to be tested

A clinician-focused, spaced learning pain assessment performance feedback intervention (‘intervention’) combining: (1) an online spaced learning module delivering authentic case-based cancer pain assessment scenarios directly to participants’ mobile devices; (2) real-time site-specific pain assessment audit and feedback, providing de-identified peer-to-peer comparisons; and (3) online links to evidence-based pain assessment decision supports.

#### Development of the intervention

The research team has undertaken a program of work [30, 31], underpinned by the Medical Research Council’s (MRC) Framework [32] for complex interventions, to better understand and address the cancer pain assessment evidence practice gap. The development phase involved an environmental scan, review of cancer patient reported pain ratings, audit of cancer pain assessment practices and development of a tailored mHealth intervention designed to increase cancer and palliative care clinicians’ capacity to effectively screen and comprehensively assess their patients’ cancer pain. This mHealth intervention integrates several evidence-based elements, namely: (1) spaced learning; (2) audit and feedback and use of a clinical champion; and (3) a theoretical framework (COM-B System) (Fig. 2).

**Fig. 2 Fig2:**
[figure not shown]
Applying the COM-B system to the CPAS trial

#### Spaced learning

Learning encounters which are ‘spaced’ and ‘repeated over time’ (‘spaced learning’) result in more efficient learning and improved retention compared to the traditional face-to-face bolus distribution learning format [33, 34]. A recent systematic review has identified that when delivered prospectively, spaced learning generates significant topic-specific knowledge [35]. Spaced learning differs significantly from other pedagogies in that it ‘pushes’ short, clinically focused, case-based scenarios to a participant’s email, which take ≤ 5 min to answer every other day. Upon answering a question, a participant’s de-identified performance is compared to that of their peers and they are provided with succinct feedback and links to relevant evidence-based resources and decision supports. The spaced learning cancer pain assessment case-based learning scenarios were developed by an expert panel comprising palliative and cancer care clinicians as well as education specialists, using the CASE methodology, a systematic framework for generating evidence-based, authentic case scenarios for learning [36]. These case-based learning scenarios have been tested in our pilot and feasibility studies [30, 31].

#### Audit and feedback

There is moderate evidence that auditing professional practice and feeding back the results encourages greater adherence to professional standards and/or guidelines [28]. A recent RCT demonstrated the value of integrating actual performance data into interventions designed to change clinicians’ behaviour in a simulated environment [37]. The quality and safety data feedback, as part of a spaced learning intervention, impacted positively on US surgical residents’ knowledge retention and simulated central line insertion performance [37]. While there is ample RCT evidence that spaced learning can improve knowledge acquisition and increase knowledge retention from three months and up to two years [33, 34, 37]), there are no robust data that spaced learning can impact positively on clinical practices outside of a simulated environment [35]. In our intervention, real-time site-specific pain assessment audit and feedback, providing de-identified peer-to-peer comparisons will be integrated into the spaced learning case scenarios. As there is good evidence that audit and feedback is most effective when provided by a supervisor or colleague (‘clinical champion’) [28], the photo and a statement from the site-specific clinical champion will also be integrated into the case scenario feedback script. Participants will be provided with hyperlinks to evidence-based pain assessment decision supports.

#### Theoretical framework

The intervention is underpinned by the COM-B System (Fig. 2), a framework for understanding and targeting behaviour change [27]. In this framework, capability, opportunity and motivations interact to generate the desired clinical behaviour. In this study, clinicians’ capabilities include having the necessary knowledge and skills to routinely screen for pain and to proceed to complete a comprehensive pain assessment if the patient reports a NRS pain ≥ 3. Motivation energises and directs clinician behaviour including conscious decision-making about routine screening and assessing to make cancer pain screening and assessment possible. Opportunity includes all factors that lie outside of the individual that prompt clinicians to make cancer pain screening and assessment possible (access to online decision prompts and strategies for integrating pain assessment into usual care). Adopting the evidence-based spaced learning pedagogy adds strength to this theoretically driven behaviour-change intervention. The Qstream™ platform will be used to deliver the spaced learning case-based cancer pain assessment scenarios and relevant site-specific pain assessment performance data.

#### Pilot testing

The piloting phase tested the acceptability of the spaced learning intervention [30] and the feasibility of the proposed RCT [31]. Our uncontrolled pilot demonstrated a significant reduction in the mean patient-reported average daily numerically rated pain scores (0–10), between the pre-post test audit, of 1.5 (95% confidence interval [CI] = 0.7–2.3) [30]. In our pre-post test feasibility study, a positive effect was observed in all measures in the study. A larger adequately powered RCT is required to confirm these results given these previous studies had insufficient power to demonstrate statistical significance. These pilot study results have informed the proposed RCT sample size [30, 31]. This manuscript focuses on the protocol for the evaluation phase, which aims to determine if a tailored online spaced learning intervention that increases clinicians’ cancer pain assessment capabilities translates into a clinically significant reduction in cancer and palliative care patients’ NRS pain scores.

#### Intervention arm

Consenting participants randomised to the intervention arm will receive the intervention immediately (Fig. 3). During the intervention, the participants will receive four real-time site-specific pain assessment audit and feedback data-related questions as well as eight case-based cancer pain screening and assessment scenarios (‘case studies’). The intervention will be delivered via Qstream™, the online spaced learning platform. Each case will be delivered directly to participant’s mobile devices (via a free app) or email. Participants will receive two case studies every second day, with each case taking approximately 3–5 min to answer. Upon answering a case, participants will receive: immediate de-identified feedback on how they have performed compared to their peers; and/or succinct audit and feedback data regarding their sites pain screening or assessment practices, with site-specific messages from local clinical champions. They will also receive links to relevant evidence-based resources and the Australian Cancer Pain Management in Adults Guidelines decision support [12]. Correctly answered cases will be re-sent after eight days, incorrectly answered cases will be re-sent every five days. Cases will no longer be sent once they have been correctly answered twice. While the study period for each participant will vary depending on how long it takes them to complete the intervention, it is estimated that it will take no longer than four weeks, as detailed in Fig. 3.

**Fig. 3 Fig3:**
[figure not shown]
Standard Protocol Items Recommendations for Interventional Trials (SPIRIT) figure [5] showing the schedule of enrolment, interventions and assessments for the Cancer Pain Assessment Study Trial

#### Control group

Consenting participants randomised to the wait-listed control group will complete all of the data collection measures but will not have access to the intervention until the intervention arm participants at each site have completed the trial and all data collection has been completed. It is anticipated that the control group participants will have access to the intervention within 16 weeks of the trial commencing at each site.

#### Adherence to intervention

Intervention adherence will be monitored weekly via reporting analytics built into the QStream™ platform. All participants will receive notification via their nominated email and/or app, when a new case study is available to answer, and/or if there are case studies awaiting their completion. Weekly engagement reports will be generated via the Qstream™ platform to monitor participants’ progress. Participants who are not progressing through the intervention as planned will be emailed directly and offered online or face-to-face technical support, as required. Participants’ individual progress will remain confidential and will not be disclosed to the participating service; however, de-identified, weekly progress reports will be sent to the each site’s nominated ‘clinical champion’ to identify the percentage of participants who have enrolled and completed the intervention. The research team will be available to assist participants with any technical aspects of the intervention, such as app download, and help troubleshoot any other technical issues that may arise.

### Outcomes

#### Primary outcome measure

The primary outcome measure will be at the patient level and concern the probability that a tailored mHealth performance feedback intervention will translate to a clinically meaningful reduction in the mean change in the pain NRS (0–10) scores, from admission to census date. A cut-off of a two-point difference or 30% reduction in pain intensity on a NRS is considered to represent a clinically important difference [38].

As this is a pragmatic trial, all pain NRS scores will be captured during the chart audit process from the patients’ medical records, thus negating the need for patient consent. The NRS is the optimal brief measure of pain severity on the basis of compliance rates, responsiveness, ease of use and applicability; it is also recommended by the Australian Cancer Pain Management in Adults Guidelines [12]. The inter-rater reliability of the chart auditors will be calculated using: Kappa statistics for categorical variables; and the Bland–Altman method of plots and limits of agreement for continuous variables will be used to determine the degree of agreement between chart auditors [39]. A waiver of patient consent has been authorised by the Human Research Ethics Committee (HREC) to include documented de-identified pain screening and assessment data from all patients receiving care from the participating units/sites during the a priori defined audit periods at Times 1–3, to avoid selection bias.

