## Background

Effective pain management cuts across professional boundaries with clinicians’ failure to routinely screen and assess for pain contributing to the burden of unrelieved cancer pain experienced by 39–66% of cancer patients [1]. To date, most research has focused on testing new cancer pain treatments, with little attention payed to strengthening cancer pain screening and assessment practices. Evidence suggests that implementing routine screening and assessment and managing pain in accordance with evidence-based guidelines can improve quality of care and outcomes for cancer pain [2–4].

Evidence of screening and assessment practices are increasingly being recognised as quality indicators of optimal cancer pain management internationally, with pain now recognised as the fifth vital sign and routinely recorded on inpatients’ observation charts [5]. The subjective nature of pain makes measuring patient-reported outcomes the optimal source of clinical information [6]. However, instead of routinely seeking a patient-reported Numerical Rating Scale (NRS) pain score, many clinicians adopt informal pain screening approaches [7] and/or fail to comprehensively assess their patients’ pain [8, 9]. A survey of Australian patients receiving community palliative care found that one-third experienced moderate to severe pain, restricting their activities over the preceding three days [10]. When this survey was repeated with a different cohort, a similar burden of unrelieved pain was reported [11].

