### Secondary objectives

To determine if the intervention:i.increases clinicians’ adherence to the Australian Cancer Pain Management in Adults Guidelines’ screening and assessment recommendations;ii.increases the quality of clinicians’ pain assessment documentation;iii.increases clinicians’ cancer pain assessment capabilities (knowledge and confidence); andiv.is cost-effective compared with standard cancer and palliative clinician CPD activities at reducing cancer patients’ reported pain scores from a healthcare systems perspective.

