### Blinding

Study investigators are blinded to participant allocation; however, project officers collecting and managing the data will not be blinded, as the frequency of documented pain assessment between the intervention and control groups is a secondary outcome measure in this RCT.

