##### Chart audit data

Patient-reported pain NRS scores and clinicians’ adherence to pain screening and assessment guidelines will be extracted from patients’ inpatient/ambulatory care medical records (electronic and/or paper-based). The chart audit tool developed, tested and refined during the pilot studies will be adopted to ensure standardised data collection. Medical records of all patients in the participating units, over 30 consecutive calendar days, will be screened for audit at each study time period (T1–T3). This will facilitate capturing chart audit data within the same duration across all participating units at each study time point. Documented patient-reported pain NRS scores and guideline adherence data will be collected by trained project officers.

Eligible medical records (chart audit) will include all patients who during the three audit periods: (1) have a primary diagnosis of cancer; 2) present for cancer treatment at a participating centre and/or are referred to a specialist cancer/palliative care service; and (3) have pain at the time of first visit/appointment/admission or develop pain during the audit period. In addition to capturing patients’ basic demographics such as age, gender, length of hospital stay, medical diagnosis, and cancer and pain treatment(s), the chart audit will also capture: patients’ pain scores on admission to the service; their pain scores at discharge and/or audit date, depending on which occurs first; clinicians’ documentation pain screening/assessment actions; and whether the clinician who documented the pain screening/assessment actions was an intervention participant or non-participant (T2 and T3 only).

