#### Statistical methods

##### Statistical analysis plan

An intention-to-treat analysis will be applied to all primary and secondary outcomes. Missing data will be imputed using Multiple Imputation by Chained Equations. Should an imbalance in clinicians’ characteristics be found between groups at baseline, these characteristics will be included in the final analyses as covariates. A significance level of 5% will be adopted for refuting all test hypotheses. The intervention and wait-listed control arms will be compared on the primary and secondary outcome measures.

The primary endpoint (reduction in mean pain NRS scores) will be analysed using the Linear Mixed Method with a repeated measures approach and possible adjustments to patients’ and staff characteristics to compare the mean change in patient pain NRS scores from admission to discharge or audit date between the intervention and control groups across different time points.

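### The primary NRS is whatever clinicians charted, and the intervention aims to change charting, so recording can bias the pain comparison in an unknown direction that standard imputation would not remove

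*Protocol article*

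**What the plan says.** All quotations are from the protocol article.

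- **Source of the outcome.** Under Primary outcome measure, "all pain NRS scores will be captured during the chart audit process from the patients’ medical records". Chart audit data adds that "Documented patient-reported pain NRS scores and guideline adherence data will be collected by trained project officers". The scores wanted are one at admission and one at discharge or audit date, from inpatient or ambulatory records.
- **Usual practice.** The Background says that, "instead of routinely seeking a patient-reported Numerical Rating Scale (NRS) pain score, many clinicians adopt informal pain screening approaches". The same section also describes "pain now recognised as the fifth vital sign and routinely recorded on inpatients’ observation charts".
- **Target of the intervention.** The first secondary objective asks whether it "increases clinicians’ adherence to the Australian Cancer Pain Management in Adults Guidelines’ screening and assessment recommendations". The Theoretical framework section counts among the capabilities it targets "having the necessary knowledge and skills to routinely screen for pain". The Blinding section confirms that "the frequency of documented pain assessment between the intervention and control groups is a secondary outcome measure in this RCT".
- **Missing data.** The Statistical analysis plan section says "Missing data will be imputed using Multiple Imputation by Chained Equations". It analyses the mean change in NRS from admission to discharge or audit date, between arms and across time points.

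**The concern.** The trial expects its intervention to alter the process that generates its primary outcome. If clinicians in one arm begin to ask and chart routinely while those in the other continue informally, the recorded scores in the two arms are differently selected samples of the patients' true scores. The means can then differ although pain does not.

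The safeguards in the article address other problems. Kappa, Bland–Altman limits and the 10% second audit test whether a charted score was copied correctly, not whether one was taken. The selection-bias remark under Primary outcome measure concerns the waiver of patient consent. Chained-equation imputation, as normally applied, predicts a missing score from observed variables. It does not correct for missingness that still depends on the unseen score once those variables are taken into account.

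At stake is whether a difference in the primary analysis can be called pain reduction. The responder rate that feeds the cost-effectiveness model is open to the same distortion.

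**Working it through.** **Inputs from the article.** The target difference is 1.5 and the bracketed 2.0 is read as an SD (Sample size). The endpoint is change from admission. No recording rate is given, so there is no completeness figure to reproduce.

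**Assumptions.** True pain is the same in both arms. Scores are normal with SD 2.0, rounded and limited to 0–10; admission mean 5, second-score mean 3, correlation 0.5. Second scores of 3 or more are recorded 90% of the time in both arms. Second scores below 3 are recorded 90% of the time in the intervention arm and 30%, 50% or 70% in control.

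**Step 1, second score alone.** The recorded mean is Σp(x)w(x)x / Σp(x)w(x), where p is the true distribution and w the recording probability.
- Scores 0, 1 and 2 have probabilities 0.1056, 0.1210 and 0.1747, in total 0.4013. Their mean is (0.1210 + 2 × 0.1747)/0.4013 = 1.172.
- The overall mean is 3.056, so scores of 3 or more average (3.056 − 0.4013 × 1.172)/0.5987 = 4.318.
- Intervention arm: equal weights leave the mean at 3.056.
- Control at 50%: (0.4013 × 0.5 × 1.172 + 0.5987 × 0.9 × 4.318)/(0.4013 × 0.5 + 0.5987 × 0.9) = 2.562/0.7395 = 3.46.
- Artefact: 3.06 − 3.46 = −0.41.

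**Step 2, the planned change score.** Patients with a recorded second score in control also have higher admission scores, because the two correlate, so part of the artefact cancels in complete cases. Imputing missing second scores from admission NRS within arm brings every admission score back in, but predicts control second scores that are too high. Less then cancels. Intervention minus control:

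| Low second scores recorded in control (intervention 90%) | Second score alone | Change, complete cases | Change, after imputation | Change, complete cases, admission equally selective |
|---|---|---|---|---|
| 30% | −0.69 | −0.34 | −0.55 | −0.23 |
| 50% | −0.41 | −0.20 | −0.32 | −0.12 |
| 70% | −0.18 | −0.09 | −0.14 | −0.05 |

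As a share of the 1.5-point target, 0.09/1.5 = 6% and 0.55/1.5 = 37%. With the second-score mean at 2.5 or 3.5, the change artefact spans 0.08–0.37 in complete cases and 0.13–0.61 after imputation.

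**Step 3, a different recording model.** Let the log-odds of recording rise by 0.25, 0.5 or 0.75 per NRS point, with overall recording of 50% in control and 90% in intervention and a second-score mean of 3.5.
- Only the second score selective: the change artefact is −0.19, −0.33, −0.41 in complete cases and −0.28, −0.51, −0.67 after imputation.
- Harsher case, 40% against 90% at the steepest slope: −0.52 and −0.86.
- Admission equally selective, 50% against 90%: about 0.0 in complete cases and −0.09 to −0.16 after imputation.
- Recording of 90% against 95%: at most 0.05 in complete cases and 0.08 after imputation.
- Recording unrelated to pain: zero.

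**Step 4, opposite selection.** Return to the model of Step 1, but let control miss the higher scores: 50% of scores of 3 or more recorded, 90% of lower ones. The same formulas give +0.46 on the second score, +0.23 on change in complete cases and +0.35 after imputation. This works against the intervention.

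**The case against.** A reader might infer that the bias must favour the intervention, that it could reach about half of the 1.5-point target (0.77/1.5), and that it would produce a false positive in 38% of trials with 45 units per arm. The documents do not support that reading.

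- Those figures concern the second score alone and come from the harshest recording gap (0.77 is at a second-score mean of 2.5; the 38% assumes a 0.7-point shift). The endpoint is a change, on which the artefact is smaller.
- Nothing in the article says that low scores are the ones left uncharted. The Abstract describes cancer pain as under-recognised, and the Background lists patients not reporting pain as a barrier. Better screening could therefore uncover higher scores and bias the comparison against the intervention.
- A score need not depend on a clinician choosing to ask. The Background says pain is routinely charted for inpatients, which could make the problem small there. Ambulatory records are also used, and the article names no source within the record.
- Clinicians are randomised individually, and the only stated link between chart and arm is who documented the screening or assessment action. A score that nobody recorded has no stated arm, so missingness by arm is not yet defined. This objection stands and shapes the fix.
- A statistical analysis plan not shown here may already hold not-at-random sensitivity analyses, and their absence from an article is not in itself a fault. Such analyses would only probe the problem, though. What counts as the outcome score is fixed at data capture, and a score never taken cannot be recovered.

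**Conclusion.** The point holds as a conditional one. Each step to outcome-dependent recording that may differ by arm has support in the article, except which scores go unrecorded, on which it is silent. Sign and size are therefore unknown. If low second scores are missed in control at the assumed rates, the spurious benefit on the change score is roughly 0.1–0.3 points in complete cases and 0.1–0.6 after imputation. It shrinks if admission scores are equally selective, is near zero if recording is about 90% in both arms or unrelated to pain, and reverses if higher scores are missed. These figures rest on the assumed means, correlation and recording rates. They also assume that imputation is done under missing at random, which the article neither states nor rules out. The mechanism alone could not easily produce the full 1.5-point target, but it could account for a material part of a smaller observed difference, or hide one.

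**What to change.** 1. **Primary outcome measure and Chart audit data.** Take both the admission score and the discharge or audit-date score by one fixed source-and-time rule. An example is the routine observation chart for inpatients, with a visit-based equivalent for ambulatory records. Apply it identically in both arms and do not restrict it to scores charted by participants.
2. **Arm of a chart.** Assign each chart to an arm by a rule that does not depend on whether a score was recorded.
3. **Reporting.** Give the share of eligible charts with each score, by arm and time point.
4. **Statistical analysis plan section.** Add a delta-adjusted not-at-random sensitivity analysis that shifts imputed scores upwards and downwards, separately by arm, over a range fixed in advance. Describe a positive primary result as pain reduction only if it survives the plausible part of that range.

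The cost is a change to the audit tool and its instructions, one completeness table and one sensitivity analysis. Ambulatory records will take some extra work. The price in interpretation is a weaker claim if completeness proves to differ by arm; if it is high and balanced, the primary result is stronger.
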